# STATEMENT OF COMPLIANCE

This document is a protocol for a clinical research study. The study will be conducted in compliance with all stipulations of this protocol, the conditions of ethics committee approval, the NHMRC National Statement on Ethical Conduct in Human Research (2007) and the Note for Guidance on Good Clinical Practice (CPMP/ICH-135/95).

# PROTOCOL SYNOPSIS

| Title | The protective effect of remote ischaemic preconditioning in congenital heart disease patients undergoing cardiopulmonary bypass surgery |
| --- | --- |
| Objectives | Support of the circulation during heart surgery using the heart-lung bypass machine is inevitably associated with organ damage and associated reduced function. This is due to reduced blood flow (ischaemia), the effects of restoration of flow (reperfusion injury) and the subsequent inflammation that is caused. The body has its own way of protecting itself against reduced blood flow and oxygen by a mechanism known as preconditioning. In essence, brief periods of mild ischaemia are protective against a subsequent more severe episode of ischaemia. These periods of mild ischaemia can be of the organ itself or of another organ in the body. For example ischaemia of the leg can protect the heart against ischaemia, so called “remote preconditioning”. We have shown in animal and human models that remote preconditioning using a tourniquet placed around a thigh for brief periods (similar in duration to when taking blood samples from children) reduces the amount of injury to heart muscle by 50% and also leads to improved heart and lung function. We have shown that remote preconditioning in a similar way protects the organs of a heterogeneous group of children undergoing cardiac surgery, resulting in better function of the heart and lungs and also a reduction of the inflammatory response to the heart-lung machine. This could potentially reduce the problems in looking after children after surgery and also reduce the amount of time spent in the intensive care unit.  We will study a more uniform group of patients undergoing cardiac surgery in the neonatal period inorder to identify key protein and metabolic changes that occur within this cardioprotective protocol. All interventions will be performed during the period of routine general anaesthesia at the time of surgical repair. We will study the degree of organ injury induced by heart-lung bypass using standard intensive care parameters and equipment for measuring lung function. The degree of heart muscle and blood cell metabolic function will be assessed by laboratory tests. Samples will be taken from routinely discarded resected cardiac tissue and indwelling catheters routinely placed at the time of surgery and not require additional venepuncture. Measurements will be made prior to surgery and also at set time intervals in the first 24 hours postoperatively to determine the evolution of effects. |

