
- 1. **Research Question**

Based on the above background and our previous studies, we will endeavour to identify a plasma-borne factor produced by brief repetitive episodes of ischemia-reperfusion (IPC) in the thigh that induces a protective state in remote organs (remote ischemic preconditioning, RIPC). We will assess the global proteomic and mitochondrial metabolic response to IR injury in children undergoing heart surgery with CPB and the modification of such a proteomic response induced by remote IPC stimulus. Proteomic assessment and mitochondrial metabolism methodology will be employed concurrently.

- 1. **Rationale for Current Study**

We hypothesise that brief repetitive episodes of ischemia and reperfusion in the thigh release a plasma-borne factor that induces a protective state in remote organs and significantly modifies systemic inflammatory response to IR injury and modulates mitochondrial metabolic function in heart muscle and lymphocytes. These effects may afford augmented organ protection to neonatal children undergoing cardiopulmonary bypass surgery. Characterization and identification of the remote IPC protective factor and pathways that foster recruitment of innate protective mechanisms against organ dysfunction following IR injury will be crucial to tailoring more efficient and clinically practical protective therapy. The future clinical application of such protection could be immense and may ultimately encompass organ transplantation, protection against stroke, myocardial infarction, acute multi-organ dysfunction, and attenuation of systemic inflammatory response in diverse clinical scenarios.

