**5.1.1 Description**

The hypothesis will be tested in children with tetralogy of Fallot undergoing elective open heart surgery with standard heart arrest and cardiopulmonary bypass. An informed consent will be obtained from all the patients’ parents or guardians. 40 patients will be recruited in to the study within two years. They will be randomized into 2 equal sized groups: Group I control (Sham, n=20) and Group II preconditioning (RIPC, n=20).

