# SUBJECT ENROLLMENT AND RANDOMISATION

- 1. **Recruitment**

Patients will be recruited by either the surgeon ([name]) or cardiologist ([name]) at the preadmission clinic or on the ward prior to surgery. The clinician ([name]/[name]) will explain to the patient’s parents/guardians, the research project, their child’s role, and outcomes and will obtain signed consent if granted.

- 1. **Eligibility Criteria**
     1. **Inclusion Criteria**

Patients with tetralogy of Fallot aged one month and older (to 18 years) having surgery for the first time.

- - 1. **Exclusion Criteria**

Patients with chromosomal defects, associated congenital lung malformations and haematological disorders will be excluded.

- 1. **Randomisation Procedures**

Random allocation is made in blocks in order to keep the sizes of the 2 treatment groups similar. In order to avoid predictability, the block size that is randomly selected is 2, 4 or 5, as the sample size must be divisible by the block size. Due to the expected relative uniformity of condition in the patient group and the small number of subjects the design will not be stratified. The randomisation will be performed in secret by a member from Heart Research (not involved in working for the trial) using SPSS statistical software generated randomisation and will place each designation sequentially in numbered envelopes 1 to 40, for patient 1 to 40 and the envelopes will be signed and sealed. The implementer of the RIPC or Sham co ntrol treatment protocols will open one envelope in numerical order immediately prior to placement of the blood pressure cuff and they will apply the RIPC treatment or sham control protocol accordingly.

- 1. **Blinding Arrangements**

[name] will not be blinded as she will be applying the RIPC treatment. She will also be involved in randomisation, sample collection, data collection, data entry and laboratory analysis. Surgeons, perfusionists, anaesthetists will be blinded. Samples will be de-identified and therefore, research laboratory staff will be blinded to the patient’s identity. The blood pressure cuff will be positioned on the thigh for both sham control and RIPC groups, however if other theatre staff witness whether the RIPC treatment protocol is invoked they will not be blinded. As these theatre staff are strictly performing standard clinical tasks and procedures and are not involved in the trial and analysis *per se*, this should not impact the blinding.

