**10.2 Population to be analysed**

The subjects are recruited and consented tetralogy of Fallot patients undergoing first time corrective surgical palliation.

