**10.3 Statistical Analysis Plan**

Lab Assay analyses will be performed on coded samples by Drs [name] and [name] and the values then made available for statistical testing when all tests are complete. Statistical analyses will be performed by Drs [name], [name] & [name]. An independent professional statistician experienced in trials will be employed to check and verify the analyses prior to and after breaking the blinding. In addition to two-way ANOVA or unpaired t test, statistical analysis will employ stepwise multivariate regression and analysis of covariance tests in order to determine potential influence of age, gender, bypass time, drugs, body weight and other morphometric and clinical factors.

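### The synopsis and, more loosely, the rationale speak of neonates, but eligibility runs from one month to 18 years; the wording must be reconciled and age made a fixed covariate rather than a stepwise candidate

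*Protocol*

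**What the plan says.** **Neonatal wording.** The Protocol Synopsis says: "We will study a more uniform group of patients undergoing cardiac surgery in the neonatal period". The Rationale for Current Study says the effects may offer "augmented organ protection to neonatal children undergoing cardiopulmonary bypass surgery".

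**Governing population.** The Inclusion Criteria read: "Patients with tetralogy of Fallot aged one month and older (to 18 years) having surgery for the first time". Section 5.1.1 says: "The hypothesis will be tested in children with tetralogy of Fallot undergoing elective open heart surgery". Section 10.2 says: "The subjects are recruited and consented tetralogy of Fallot patients undergoing first time corrective surgical palliation". Neither 5.1.1 nor 10.2 has a neonatal limit.

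**Stratification.** Randomisation Procedures gives two reasons for not stratifying. The first is "Due to the expected relative uniformity of condition in the patient group"; the second is the small number of subjects.

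**Age in the analysis.** Section 10.3 starts from two-way ANOVA or the unpaired t test. It adds stepwise multivariate regression and analysis of covariance "in order to determine potential influence of age, gender, bypass time", drugs, body weight and an open list of other factors.

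**The concern.** A reader who relies on the synopsis would expect a narrow neonatal cohort. The criteria admit a range from one month to 216 months (18 × 12) and leave neonates out. Two things are at stake.

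The first is the target of inference. A report that carried over the synopsis wording could claim relevance to patients whom the trial cannot enrol.

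The second is how age enters the treatment comparison. With 20 patients per arm and so wide a range, the arms may differ in age by chance. Under a stepwise procedure, the data decide whether age is in the model, so the adjusted comparison is not fixed before the results are seen.

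**Working it through.** **1. Passages side by side (Protocol).**

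| Place | Population described |
| --- | --- |
| Synopsis | more uniform group, surgery in the neonatal period |
| Rationale | possible benefit to neonatal children |
| Inclusion Criteria | tetralogy of Fallot, one month to 18 years, first surgery |
| 5.1.1 | children with tetralogy of Fallot, elective open heart surgery |
| 10.2 | tetralogy of Fallot, first-time surgery |

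If neonatal means about the first 28 days, its overlap with one month and older is empty. The synopsis cannot be read consistently with the criterion. The rationale conflicts more loosely, because it speaks of who may benefit rather than who is enrolled.

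**2. Does a stated figure depend on the neonatal wording?** No. The only sample size in 10.1 with all its inputs is for mitochondrial oxygen consumption: difference 20%, sigma 14.5 (read as percentage points, an assumption), power 0.8, alpha 0.05 (taken as two-sided).

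- Normal approximation: n = 2 × (1.96 + 0.84)² × (14.5/20)² ≈ 8.3, so 9 per group.
- Exact t test: 9.3, so 10 per group. This reproduces the stated 10, read as per group.

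Age wording does not enter this calculation.

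**3. Chance imbalance in an age band.** Inputs: 40 patients, 20 per arm (5.1.1), no stratification. Let K be the number of patients in one age band. The documents give no age distribution, so K is an assumption. Blocking fixes the arm totals but ignores age. If arrival order is unrelated to age, the number k of band members in one arm is hypergeometric:

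P(k) = C(K,k) × C(40−K, 20−k) / C(40,20)

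For K = 20, the probability of a 12:8 or worse split is 1 − [P(9) + P(10) + P(11)]:

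1 − (167,960² + 184,756² + 167,960²) / 137,846,528,820 = 1 − 0.657 = 0.343

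| K of 40 (assumed) | Split | Probability |
| --- | --- | --- |
| 20 | 12:8 or worse | 0.343 |
| 20 | 13:7 or worse | 0.113 |
| 10 | 7:3 or worse | 0.273 |
| 10 | 8:2 or worse | 0.065 |

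**4. The same on a continuous scale.** The standard error of the standardised difference in mean age is √(2/20) = 0.316. By normal approximation, a difference above 0.3 SD has probability about 34%, and above 0.5 SD about 11%.

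**5. What an imbalance could do.** If age (on the modelled scale) has within-arm correlation ρ with an outcome, an age imbalance of d SD shifts the unadjusted difference by ρ × d outcome SD. The documents give no ρ. Since |ρ| cannot exceed 1, d = 0.5 shifts the difference by at most 0.5 SD. The planned mitochondrial difference is 20/14.5 = 1.38 SD. The possible distortion is therefore moderate, and smaller for any realistic ρ.

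**6. Cost of a fixed age term.** For a comparison at one time point with complete data, residual degrees of freedom go from 40 − 2 = 38 to 40 − 3 = 37.

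**The case against.** The strongest reply is that this is a wording slip. The objectives, hypotheses and aims speak of patients undergoing congenital heart surgery. Sections 5.1.1 and 10.2 and the Inclusion Criteria all define the cohort by tetralogy of Fallot, and no endpoint or analysis makes a neonatal claim. This largely stands: the contradiction is certain, but it sits in descriptive text and correcting it is close to editorial.

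A reader might infer more, namely that the uniformity behind the unstratified list fails. The protocol does not support that. Randomisation Procedures relies on uniformity of condition, not of age. One diagnosis, first surgery and the exclusion of chromosomal, lung and haematological disorders support it. The small number of subjects is a separate reason that stands by itself. In the synopsis, more uniform is relative to an earlier heterogeneous group of children. The undefined age-groups in the gel analysis (8.1.4) do not show that age heterogeneity was planned for either; they may be a wrong label for the treatment groups.

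The imbalance probabilities are ordinary chance imbalance, which any binary covariate would show, under an assumed age mix. The 5% error rate of an unadjusted test already allows for it. That stands too, so the figures show a risk worth handling, not a bias in the design.

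It would also be wrong to say that age enters only by stepwise selection, because 10.3 names analysis of covariance as well. An SAP, not shown here, may fix the covariates. What remains is that the protocol itself names a stepwise method and frames both methods as exploring possible influences. It does not commit age to the RIPC versus sham comparison.

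**Conclusion.** The point holds in two limited parts.

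- **Population wording.** The neonatal wording contradicts the age criterion and must be reconciled. This rests only on the usual meaning of neonatal. No conclusion specific to neonates can be drawn from the trial.
- **Handling of age.** With ages from one month to 18 years and 20 per arm, a fixed age term is a better method than stepwise candidacy, at almost no cost. The risk it addresses is moderate: about 34% for a 12:8 or worse split if half the patients are in one band, and 27% for 7:3 or worse if a quarter are. Both age mixes are assumptions, and the effect on any outcome depends on a correlation that the documents do not give.

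The lack of stratification is not a defect, and no stated sample size is affected.

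**What to change.** 1. Reconcile the Synopsis and the Rationale with the Inclusion Criteria. Sections 5.1.1 and 10.2 and the criteria already agree on diagnosis, so changing the descriptive text is the smallest correction, once the sponsor confirms the intended population. Make no claim specific to neonates in the report.
2. In Randomisation Procedures, say that the expected uniformity is one of diagnosis and first surgery, not of age. Keep the small-numbers reason. The list need not be stratified.
3. In 10.3, prespecify age as a fixed covariate in the main RIPC versus sham comparisons and remove it from the stepwise candidates. State the transformation in advance; a log scale is natural for a 216-fold range, since otherwise a few adolescents would dominate the fit. Age is set before randomisation, so adjusting for it does not condition on anything that follows treatment.
4. Limit this to the main comparisons. The spot-screening t test in 8.1.4 need not be rebuilt for this purpose.

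The cost is a few sentences, about one degree of freedom per comparison, and no new data, because 10.3 already lists age.

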
# GLOSSARY OF ABBREVIATIONS

| **ABBREVIATION** | **TERM** |
| --- | --- |
| CPB | cardiopulmonary bypass |
| IR | ischemia-reperfusion |
| IPC | ischemic preconditioning |
| MI | myocardial infarction |
| RIPC | remote ischemic preconditioning |
| mmHg | millimetres of mercury, unit of blood pressure |
| CICU | cardiac intensive care unit |
| M | molar (moles/litre) |
| µM | micromolar |
| µl | microlitres |
| U | units |
| mg | milligrams |
| kg | kilograms |
| µg | micrograms |
| m2 | metre squared (unit of area) |
| O2 | oxygen |
| DIA | Differential In-gel analysis |
| nm | nanometre |
|  | Extinction coefficient |
| MPTP | Mitochondrial membrane permeability transition pore |
| MCRI | Murdoch Children’s Research Institute |
| RCH | Royal Children’s Hospital |
|  |  |
|  |  |
|  |  |
|  |  |
|  |  |
|  |  |
|  |  |
|  |  |
|  |  |

# INTRODUCTION AND BACKGROUND

- 1. **Background Information**

Patients undergoing heart surgery with standard cardiac arrest and cardiopulmonary bypass (CPB) develop tissue injury due to myocardial ischemia and systemic inflammatory response to CPB. Paradoxically, most of the myocardial damage occurs once the coronary artery is reopened and the blood flow is restored. This phenomenon is referred to as an ischemia-reperfusion (IR) injury and associated with a systemic inflammatory response, myocardial dysfunction, and cardiac arrhythmia. Furthermore, systemic inflammatory response induces post-operative multi-organ dysfunction of various degrees that results in prolonged hospital stay and delayed recovery. Protection against IR injury is of particular importance in children undergoing heart surgery as, due the severity of heart anomalies, it often requires prolonged period of heart arrest to perform a complex repair. Such protection is also important in adult patients with decreased heart function due to recent myocardial infarction undergoing heart surgery or angioplasty.

One of the most fascinating physiological mechanisms of nature is the innate mechanism by which all living cells protect themselves from the lack or excess of oxygen that occur during IR injury. This powerful innate protection can be induced by a brief period of ischemia that precedes a prolonged, life-threatening period of ischemia. This phenomenon is known as ischemic preconditioning (IPC). The IPC reduces myocardial infarction (MI) by 60% following coronary artery occlusion (1,2) and has been shown to reduce myocardial injury following heart surgery (3). In addition to reducing IR injury, the IPC also modulates activation of inflammatory cells that are induced by the IR injury. In a novel human model, we previously showed that IPC not only prevents endothelial dysfunction but also significantly attenuates the secondary activation and inflammatory gene expression of circulating leukocytes (4, 5).

A more practical and clinically relevant form of protection is remote IPC where ischemia of one organ can induce a protected state in a distant organ (6). The magnitude of the effect of remote IPC appears to approach that of local IPC. A reduction in MI size of 65% was reported in a porcine model study by inducing ischemia of the lower limb (7). As with local IPC, the mediators and mechanisms of remote IPC remain to be fully elucidated but presumably include humoral agents as well as induction of gene expression (8-10).

[figure not shown]
We have previously demonstrated in an animal model of MI, the potential of remote IPC to reduce myocardial IR injury (11, 12). These studies demonstrated a 50% reduction in the extent of MI in the group with prior remote IPC compared to the control group (Figure 1). Remarkably, a brief limb ischemia applied during evolving MI in pigs resulted in similar reduction of MI (12). Furthermore, in an animal model of remote IPC and CPB we have shown significantly lower levels of plasma lactate, myocardial troponins and S-100B (markers of cardiac and brain injury respectively) (Figure 2), increased dynamic lung compliance, better cardiac diastolic function and a lesser requirement for inotropes in study animals as compared to controls (13,14). In addition, despite 2 hours of warm heart ischemia, none of the preconditioned animals required inotropes to wean from CPB (all controls did).

FIG 2. (From Kharbanda RK, et al. Heart 2006 Oct; 92(10):1506-11).

We have previously demonstrated in a porcine model that myocardium contributes significantly to total metabolic burden following hypothermic CPB (23) and that remote IPC significant decrease in coronary resistance and improved myocardial blood flow (15). After completion of our animal experiments, we applied the remote IPC concept in clinical practice and published world’s first clinical randomized controlled study of the remote IPC in children undergoing cardiac surgery that demonstrated significant cardio-pulmonary protection, particularly with regard to reduced post-CPB release of troponin I, lactate, S100B and reduced requirement for post-operative inotropes (16, 17). Subsequently, others confirmed protective effect of the remote IPC in patients undergoing coronary artery bypass surgery (18) and significant reduction in myocardial and renal injury after abdominal aortic aneurysm repair (30). Due to complexity of congenital heart defects, heart surgery in children is often associated with prolonged IR and CPB. This, in turn, results in extensive IR injury and systemic inflammatory response. A reproducible and powerful induction of innate protection against IR injury and CPB-induced systemic inflammatory response would be of particular benefit in this subgroup of patients. Although clinical benefits of protection by the remote IPC became apparent in the recent clinical trials (16-19, 30), the mechanisms for this clinically relevant protection remain yet to be elucidated (19-21).

From our previous work in a porcine heart transplant model significant myocardial protection could be achieved in the donor heart following transplantation into a preconditioned donor (9). The study ruled out the neurogenic mechanism of protection, as the transplanted heart was denervated, and suggested that remote IPC produces a blood-borne protective factor (9). This study also demonstrated that remote IPC induced a circulating factor in the blood that provided myocardial protection in transplanted heart. In other words, the remote IPC induced a lasting protected environment in the recipient prior to transplantation of the donor heart (i.e., the heart was not in the body during the IPC stimulus). This study suggested the presence of a humoral circulating factor in blood. We then further localized a “protective factor” and demonstrated in an animal model that remote IPC elaborated a transferable plasma-borne factor that protected mitochondrial structure and function and preserved myocardial performance following neonatal cardioplegic arrest (22). This metabolic and structural protection was associated with preservation of global myocardial performance (22). We have further studied human leukocyte functional responses in our pilot study performed in healthy human volunteers (24) and demonstrated that the remote IPC stimulus significantly decreased neutrophil adhesion, exocytosis, and phagocytosis. Our human pilot study (24) as well as our global genomic study (5) suggested that proteomic response to remote IPC stimulus will be significant. Others have also demonstrated that IPC can be abolished by inhibition of de novo protein synthesis at both transcription and translation levels (31-32). Furthermore, our previous genomic studies demonstrated significant changes in global gene expression in murine myocardium after the remote IPC stimulus (10) and in the human myocardium in children undergoing heart surgery (25). However, it remains unknown if the global genomic response observed in our previous studies results in translation of expressed genes into proteins. Over the recent year proteomic profiling has evolved as a reliable, reproducible and powerful technique of assessment of global protein expression in response to clinically relevant IR injury (33,34) and particularly CPB (35). This technique allows simultaneous assessment of expression of a great number of thematically linked proteins, including mitochondrial metabolic signalling proteins that may constitute protective pathways.

- 1. **Research Question**

Based on the above background and our previous studies, we will endeavour to identify a plasma-borne factor produced by brief repetitive episodes of ischemia-reperfusion (IPC) in the thigh that induces a protective state in remote organs (remote ischemic preconditioning, RIPC). We will assess the global proteomic and mitochondrial metabolic response to IR injury in children undergoing heart surgery with CPB and the modification of such a proteomic response induced by remote IPC stimulus. Proteomic assessment and mitochondrial metabolism methodology will be employed concurrently.

- 1. **Rationale for Current Study**

We hypothesise that brief repetitive episodes of ischemia and reperfusion in the thigh release a plasma-borne factor that induces a protective state in remote organs and significantly modifies systemic inflammatory response to IR injury and modulates mitochondrial metabolic function in heart muscle and lymphocytes. These effects may afford augmented organ protection to neonatal children undergoing cardiopulmonary bypass surgery. Characterization and identification of the remote IPC protective factor and pathways that foster recruitment of innate protective mechanisms against organ dysfunction following IR injury will be crucial to tailoring more efficient and clinically practical protective therapy. The future clinical application of such protection could be immense and may ultimately encompass organ transplantation, protection against stroke, myocardial infarction, acute multi-organ dysfunction, and attenuation of systemic inflammatory response in diverse clinical scenarios.

